### Summary Analysis

Key indicators of health and comparisons of those indicators to ALSWH statistics (where
available) that this survey aims to measure are: (1) SF-36 physical and mental health
scores; (2) BMI; (3) symptoms experienced over the previous 12 months; (4) consumption of
alcohol, tobacco, sugar, salt, caffeine, and dairy; and (5) prevalence and levels of
depression, stress, distress, and perceived control, as measured by standard scales.

### Comparative and Detailed Analyses

Comparisons between UM participants and ALSWH respondents are planned, using both simple
comparisons and comparisons weighted or normalized by age, education, and interest in
alternative treatments (to increase comparability).

Regression analyses will be performed to determine whether SF-36 scores or BMI are
associated with: (1) UM-related variables (length of UM participation, number of UM
events); (2) demographic variables (age, age of menopause, age of menarche, education
history); (3) menstruation-related attitudes and symptoms; (4) frequency of health-related
symptoms; (5) major health events experienced; (6) alcohol and tobacco consumption; (7)
sugar, salt, dairy, and caffeine consumption; (8) frequency of medical and other health
practitioner visits; or (9) scores on other standardized scales (depression, perceived
control, psychological distress, perceived stress), all of which are derived from the
questions taken from the ALSWH questionnaires.

The expected sample sizes are relatively small (200-400 respondents per item, given that
all items are optional), so any odds ratios and regression coefficients will be considered
significant if their 95% confidence intervals exclude 1.0 (for odds ratios) or 0.0 (for
regression coefficients).

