**Objective:**

This survey investigates whether the approximately 500 women associated with UM exhibit
health status significantly above the norm. As part of this investigation, questions for
a newly developed menstrual attitudes questionnaire will also be evaluated.

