**Results:**

The validity of the menstrual attitudes questionnaire will be evaluated with Cohen’s
kappa. ALSWH respondents and UM participants will be compared, using unweighted
regression or regression weighted or normalized by age, education, and interest in
alternative treatments (to increase comparability), as appropriate. Analyses will
determine whether UM-related variables (being a UM participant, length of UM
participation, number of UM events attended) are associated with: differences in the
number of major health events and health symptoms experienced; SF-36 physical and mental
health scores; body mass index; and consumption of alcohol, tobacco, sugar, salt,
caffeine, and dairy.

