### Health and Behavior Change

There is a plethora of associations between adhering to health guidelines and better
health outcomes, as described in a major ALSWH report [19]. The report shows that women appear to be able to reduce their intake of
clearly harmful substances (eg, smoking, alcohol; whether the latter is beneficial in
moderate doses or not) and their adherence to screenings is consistently high and stable,
or rising [19]. However, in practice it seems
currently impossible to improve people’s daily behaviors of eating less or exercising more
on a population-wide level. In fact, the opposite seems to be the case with Australians:
the percentage of overweight and obese adults is continuously increasing [18], which is a process that seems to be happening in
other countries as well [13]. Interventions that
empower women to address factors of diet, weight management, stress, and mood will likely
be most effective in improving their health.

Good health practices are well known to medical science; the issue is less one of knowing
*what* to do than knowing *how* to increase interest and
action in adopting a healthy lifestyle overall among the wider population. For example,
even diagnosis of a chronic disease (eg, heart disease, diabetes, asthma, breast cancer,
arthritis, or depression) does not lead to improved levels of physical activity [20]. Such a diagnosis in itself is not generally
adequate to induce women to improve their health behavior; although some women do make
improvements, this gain is offset by those whose behavior actually worsens [20]. Counselling from doctors has been shown to work
for high-risk patients [21], but is not being
implemented on a level that would improve population health. In addition, adherence to
doctors’ guidelines for chronic ailments is typically 50% or less [22]. A substantial group of women who are managing to adopt good
health practices would therefore be of great interest to medical science and those
responsible for public health, especially if the women’s lifestyle skills and habits are
teachable and transferable. Our goal is to study participants in a program called
Universal Medicine (UM), to determine whether they have health advantages over women at
large.

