#### The Respondent Population

The respondent population is approximately 500-600 women who, as users of complementary
medical services, may have had a similar profile to women who use alternative
practitioners (ie, more likely to be middle-aged, have poorer health, and a higher usage
of conventional medicine) [42]. On the basis of
some researchers’ observations and informal surveys, the population’s average age is now
in the high 40s, they have lost substantial weight since joining UM activities, and may
have higher than average levels of vitality.

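### The only adjusted UM-versus-ALSWH comparison named also weights on interest in alternative treatments, so no named adjusted estimate keeps women at large as the reference

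*Protocol article*

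**What the plan says.** The aims refer to a general reference group. The Abstract (Objective) asks whether UM women show "health status significantly above the norm". The Introduction (Health and Behavior Change) gives the goal as studying participants in "Universal Medicine (UM), to determine whether they have health advantages over women at" large. The Objectives section names ALSWH respondents as the comparator.

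On the analysis, the section Comparative and Detailed Analyses opens with the unadjusted contrast: "Comparisons between UM participants and ALSWH respondents are planned, using both simple" ones. The adjusted contrast follows, as "comparisons and comparisons weighted or normalized by age, education, and interest in" a third variable, which is given with its reason as "alternative treatments (to increase comparability"). The Abstract (Results) offers the same pair, unweighted "regression or regression weighted or normalized by age, education, and interest in" alternative treatments, and leaves the choice between them to judgement. Age, education and interest in alternative treatments always appear together. No comparison on age and education alone is named in either place.

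The Respondent Population says that UM women, being users of complementary services, may have had a profile like that of women who use alternative "practitioners (ie, more likely to be middle-aged, have poorer health, and a higher usage" of conventional medicine.

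**The concern.** The two named comparisons differ in two respects at once. The simple one uses all ALSWH respondents, which is the right reference for the stated aim, but leaves age and education unadjusted. The weighted one adjusts for both but also matches on interest in alternative treatments. UM women are described as users of complementary services, so that interest is probably very common among them. Weighting ALSWH to resemble them therefore moves the comparator towards women drawn to alternative treatments.

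The adjusted estimate then answers a different question: whether UM women are healthier than similarly minded women. If those women are less healthy than average, UM women no healthier than women at large could look better than the norm. Data collection is already complete and the protocol does not say which comparison carries the conclusion, so a reader could take the weighted result as the answer to the general question.

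**Working it through.** The protocol gives no effect size or power for this comparison, so there is no figure to reproduce. What follows is a sensitivity sketch.

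**Inputs from the protocol**
- SF-36 summary scores: SD 10 (Issues with the SF-36 Instrument).
- UM respondents per item: n = 200 to 400 (Comparative and Detailed Analyses).
- Significance rule: the 95% confidence interval excludes the null value (same section).

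**Assumptions (not in the protocol)**
- p: share of ALSWH women interested in alternative treatments.
- d: their SF-36 deficit against uninterested women, in points, that remains after age and education.
- All UM women are interested, and ALSWH sampling error is ignored.

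**Step 1, shift of the comparator.** If interested women have mean m and the others m + d, the ALSWH mean is p·m + (1 − p)(m + d) = m + (1 − p)d. Weighting fully to interested women lowers the comparator mean by (1 − p)d. With p = 0.3 and d = 2, this is 0.7 × 2 = 1.4 points.

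**Step 2, precision.** SE = 10/√n, which is 0.707 at n = 200 and 0.5 at n = 400. The 95% half-widths are 1.39 and 0.98 points.

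**Step 3, probability of a significant result favouring UM when UM women equal women at large.** P = 1 − Φ(1.96 − shift/SE). For a shift of 1.4:
- n = 200: 1 − Φ(1.96 − 1.98) = 50.8%
- n = 400: 1 − Φ(1.96 − 2.80) = 80.0%

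**Step 4, range.**

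| d | p | Shift | P, n=200 | P, n=400 |
|---|---|---|---|---|
| 0 | any | 0 | 2.5% | 2.5% |
| 1 | 0.1 | 0.9 | 24.6% | 43.6% |
| 1 | 0.3 | 0.7 | 16.6% | 28.8% |
| 1 | 0.5 | 0.5 | 10.5% | 16.9% |
| 2 | 0.1 | 1.8 | 72.1% | 95.0% |
| 2 | 0.3 | 1.4 | 50.8% | 80.0% |
| 2 | 0.5 | 1.0 | 29.3% | 51.6% |
| 3 | 0.1 | 2.7 | 96.8% | 100.0% |
| 3 | 0.3 | 2.1 | 84.4% | 98.7% |
| 3 | 0.5 | 1.5 | 56.4% | 85.1% |
| −1 | 0.3 | −0.7 | 0.2% | <0.1% |

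**Step 5, what age and education already remove.** Take a raw deficit of 2 points and p = 0.3. If age and education explain half of it, the extra shift is 2 × 0.5 × 0.7 = 0.7 points and P is about 17% to 29%. If they explain all of it, the shift is 0 and P is 2.5%. If interested women are healthier (d < 0), the shift works against UM.

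**Step 6, with weights on age and education only.** The interest variable contributes no shift, so in this sketch, which assumes no other bias, P is 2.5%.

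**The case against.** The case for the plan has five parts.

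- **The general contrast is kept.** The simple comparison with all ALSWH respondents is planned beside the weighted one. This stands: what is unnamed is only its age-and-education-adjusted version. A reader might infer that the plan rules that version out, but a condensed article that lists three variables does not exclude subsets of them.
- **The weighting has a legitimate purpose.** The stated reason is comparability. For separating UM from a general leaning towards alternative treatments, adding that variable is ordinary confounder control. This stands for that question, but it is not the question in the stated aims.
- **The direction is not established.** A reader might infer that the weighting inflates any UM advantage. The protocol does not support this. Its remark concerns women who use alternative practitioners, not women interested in alternative treatments, and it gives no size. It lists middle age beside poorer health, and age is already in the weights. It says only that UM women may have had such a profile. For BMI, alcohol, tobacco and diet no direction is documented.
- **Lack of overlap is not shown.** Weighting ALSWH towards UM needs ALSWH women with UM-like interest. It does not need UM women with low interest. That joining UM creates the interest is plausible but not stated.
- **The survey is exploratory.** Its conclusion bears on whether further study is worthwhile, and a 1.4-point shift is 0.14 SD. This lowers the severity.

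The mismatch remains: the unadjusted estimate has the stated reference, and the adjusted one does not.

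**Conclusion.** The point holds in a limited form. No named adjusted UM-versus-ALSWH estimate keeps the reference population of the stated aims, although the plan itself treats age and education as needing adjustment. The consequence can favour UM on general-health outcomes such as the SF-36, but need not.

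The 51% to 80% result is one assumed case among many. It depends on the chosen p and d, on full interest among UM women, and on none of the deficit being due to age or education. The documents fix none of these. The arithmetic shows only that a deficit of 1 to 3 points would matter at 200 to 400 respondents. It does not show that such a deficit exists. This is a worthwhile and cheap improvement, not an error that must be corrected.

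**What to change.** In the Abstract (Results) and in Comparative and Detailed Analyses:

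1. Name a comparison weighted or normalized on age and education only, and let it carry the conclusion about the norm and women at large.
2. Keep the version that also weights on interest in alternative treatments as a second contrast, labelled *versus women interested in alternative treatments*.
3. State that this second contrast cannot by itself support a claim of health above the norm. Add that, on the protocol's own description of users of alternative practitioners, its comparator may be less healthy than women at large.

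The simple comparison can stay as it is. No new data are needed. The cost is one more set of weights, a few lines of text, and possibly a smaller reported advantage.

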## Discussion

An important issue is that this is the first attempt to collect scientific evidence about
UM participants, and it is not even known whether the UM participants are more or less
healthy (or both in different areas of health) than the general population. This survey will
attempt to collect data to establish whether this group of people warrants further
investigation. If the group is worth investigating scientifically, the survey could generate
data that will allow the first steps of comparative effectiveness research [56,57] by
testing for associations between health outcomes and other variables. A longitudinal study
could then establish the sequence of events that lead to any associations. If these women do
not spend substantially higher sums on health care than the general population but are
markedly healthier, then this may be a pointer to insights that improve health care
economics [58].

We have chosen to construct a survey that attempts to determine whether this group of women
actually does experience exceptionally good health and, as a second step, to ascertain
whether there are any connections between the attitudes of these women regarding women’s
menstrual health issues and any aspects of their health status. The World Health
Organization states that the focus on biological health for women in medical research led to
a neglect of mental health research, with numerous negative consequences for the state of
scientific knowledge [59]. This survey, with its
coverage of physical and mental health and attitudes towards health, may allow research to
see how these three areas relate to each other in this group of women.

### Issues with the SF-36 Instrument

The scoring instructions used by the ALSWH for the SF-36 will be employed [60]. The SF-36 physical and mental health summary
scores are normalized to a mean of 50 and a standard deviation of 10. However, giving
perfect answers to every question leads to a physical score on this questionnaire of only
56.5, and a mental score of only 62.5 (for this mental score one would, for example, need
to tick *none of the time* in response to, “How often during the past four
weeks did you feel tired?”).

A further SF-36 scoring feature is that to some extent, mental and physical health scores
are mutually inhibiting. Physical health items are added as a negative score to the mental
health score and mental health items are added as a negative score to the physical health
score. This means that achievement of mental scores above 62.5 is only possible for people
with less than perfect physical health and vice versa. The best theoretically possible
mental health score can only be achieved by a person with very bad physical health and
vice versa. This may affect the usefulness of the SF-36 if many respondents actually have
a high level of both physical and mental health. One question is whether there will be a
ceiling effect, with many scores near the surprisingly low upper limits of the SF-36.

The dose-response approach proposed here uses length of association and number of events
or visits as the estimator of the UM *dose*. If results of the proposed
study suggest that this group is worth investigating further, then in a longitudinal
study, UM participants could be surveyed–perhaps in combination with objective health
measures–at or near the beginning of their association with UM, and at designated
follow-up intervals.

### Conclusions

If the surveyed women’s health is substantially better that the ALSWH cohort, if they are
easily able to maintain that improved health, and if any of their practices can be
translated in part or in whole to the general population, then investigating these women
may be very valuable for obtaining insights into improving health and quality of life, and
reducing the cost of health care in the general population.

### Ethics, Consent, and Permissions

Ethical approval CS23062015 was given by the School of Public Health Research Ethics
Committee on June 23, 2015. The first question on the survey will obtain informed consent
from all participants: “Do you give your consent to participate in this research survey?”,
with response options, “Yes, I consent to participate in this survey” and, “No, I do not
give consent.” Unless the respondent explicitly chooses *Yes*, the survey
concludes at that moment.

### Availability of Data and Materials

Deidentified data will be made available. Such data will not include potential
identifiers, as outlined in, “Preparing raw clinical data for publication: guidance for
journal editors, authors, and peer reviewers” [61]. Specifically, this means that age (which will be categorized into intervals),
lists of medical procedures undergone, and lists of major illnesses will be excluded. The
data will most likely be stored with the Open Science Framework [62].

## Appendix

Multimedia Appendix 1 ALSWH scales to which UM participants respond, and the instruments from which the
questions were derived.

Multimedia Appendix 2 Women in Livingness Survey.

## Abbreviations

ALSWH: Australian Longitudinal Study of Women’s Health
BMI: body mass index
SF-36: Short Form 36
UM: Universal Medicine
